## **6.2 Study Endpoints**

### **6.2.1 Primary Endpoint**

Changes in ketamine-induced BOLD fMRI signals in pre-specified ROIs (anterior cingulate cortex (ACC) and anterior insula) following administrations of TS-134

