8. History of recreational ketamine use, recreational PCP use, or an adverse reaction to ketamine. Subjects who have participated in prior research ketamine studies will be eligible providing they have participated in no more than 5 previous research ketamine infusions. Subjects can have infusions not more frequently than biweekly, and not more than 1/month on average, therefore subjects will need to wait 1 month if they had a single infusion and 6 weeks if they have had 2 closely spaced infusions prior to screening into the study.
9. Any subject who is unable to refrain from smoking throughout the study or with positive urine cotinine screen (> 400 ng/mL) at the Initial Screening Visit.
10. Any subject with a history and/or current evidence of serologic positive results for hepatitis B surface antigen, hepatitis C antibodies, or HIV antibodies 1 and 2 at the Initial Screening Visit.
11. History of violence, including any history of using a gun, knife, or other weapon with intent to harm someone, as well as a more than one physical fight without a weapon after the age of 18 years old (not including fights that happen during sports competition).

12. Presence or positive history of significant medical illness, including high blood pressure (SBP > 140 mmHg, DBP > 90 mmHg), low blood pressure (SBP < 100 mmHg, DBP < 60 mmHg), orthostatic hypotension (change in mean arterial pressure [ $1/3$  systolic +  $2/3$  diastolic] of > 20%) at Screening Visits (except for Final Screening Visit: Discharge) or Day -1 (Admission).
13. Any subjects who show subthreshold ketamine BOLD response (defined as % BOLD signal change of 0.5% at peak ketamine response) in ACC at Final Screening Visit.
14. Metal implants, pacemaker, other metal (e.g. shrapnel or surgical prostheses) or paramagnetic objects contained within the body which may present a risk to the subject or interfere with the MR scan, as determined in consultation with a neuroradiologist and according to the guidelines set forth in the following reference book commonly used by neuroradiologists: *Guide to MR procedures and metallic objects, F. G. Shellock, Lippincott Williams and Wilkins Philadelphia 2001*.
15. Claustrophobia.
16. Donation of one or more units of blood, plasma, or acute loss of an equivalent amount of blood within 60 days prior to Initial Screening Visit. (One unit= 450mL)

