### 9.3.5.1.3 Image Processing and Modeling

A MRI manual is being provided in a separate document to take precedence over the protocol language in this section. Any revisions to the MRI manual that are implemented during the study will be described in the final report.

No treatment identifiable information is encoded in the imaging data files and all MRI image analyses will be blinded to treatment condition. The data manager will maintain the randomization table for each imaging treatment assignment set until study database is locked.

fMRI data will be preprocessed using FSL (<https://fsl.fmrib.ox.ac.uk/fsl/fslwiki>) and Matlab (<https://www.mathworks.com/>). Preprocessing of fMRI data includes slice time correction, motion correction, spatial smoothing (5 mm full width at half maximum Gaussian kernel), and high-pass filtering with a cutoff of 1200 s will be applied to the data to minimize the influence of very-low-frequency noise and scanner drift. Linear regression is performed using 27 motion parameters including 3 translations, 3 rotations, lag +1 derivatives, lag -1 derivatives, quadratic term, the mean relative motion, and the mean absolute motion. The model residual is then used

for evaluating all ketamine-evoked responses. Linear registration to the subject's high resolution SPGR image (6 degrees of freedom) and to the MNI152 standard space template (12 degrees of freedom) is performed to generate spatial transforms.

A ROI analysis is performed using the mid-cingulate cortex, which had the largest BOLD response at 50 ng/mL ketamine in the study conducted by De Simoni. Two seeds are placed at (MNI: 4,2,42) and (MNI: -4,2,42) and spherically dilated by 8 mm. The masks are transformed to the individual subject's functional space and multiplied by the gray matter partial volume map to minimize the contribution of non-gray voxels. For each subject, the BOLD time series is extracted from the ROI and fit to a three parameter gamma model:

$$y(t) = a \left( \frac{t}{t_{\max}} \right)^{b \cdot t_{\max}} e^{(t_{\max} - t) \cdot b}$$

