## **10.5 Pharmacodynamics (PD) Analysis**

### **10.5.1 Primary Endpoint**

To evaluate the treatment effect of TS-134 on ketamine-induced BOLD signals in pre-specified ROIs (ACC and anterior insula) in resting fMRI, analysis of covariance (ANCOVA) with change from baseline at Day 6 BOLD as the outcome predicted by baseline (Final Screening Visit) BOLD and treatment in 3-treatment groups (TS-134 20 mg group, TS-134 60 mg group and placebo group) will be performed, and the mean and 95% confidence interval (CI) will be estimated. Separate ANCOVAs will be fit to each ROI. Tests of treatment effect will be made within each treatment group, between each active treatment group (TS-134 20 mg group and TS-134 60 mg group) versus placebo group, and also between the two active treatment groups from the ANCOVA. A statistically significant negative change of BOLD found in the active treatment groups compared to placebo group would be consistent with the hypothesis. Cohen's d effect sizes will be reported using the standard deviation of baseline BOLD.

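### The primary ROIs are ACC and anterior insula, but the image-processing section defines only a mid-cingulate ROI and does not tie it to either

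*Protocol*

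**What the plan says.** Protocol section 6.2.1 gives the primary endpoint as "Changes in ketamine-induced BOLD fMRI signals in pre-specified ROIs (anterior cingulate cortex (ACC) and anterior insula) following administrations of TS-134". Section 10.5.1 names the same regions, "To evaluate the treatment effect of TS-134 on ketamine-induced BOLD signals in pre-specified ROIs (ACC and anterior insula) in resting fMRI", and adds that "Separate ANCOVAs will be fit to each ROI".

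Exclusion criterion 13 in section 7.2 also depends on a regional BOLD value: "Any subjects who show subthreshold ketamine BOLD response (defined as % BOLD signal change of 0.5% at peak ketamine response) in ACC at Final Screening Visit".

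Section 9.3.5.1.3 describes how ROI values are produced. It says "A ROI analysis is performed using the mid-cingulate cortex, which had the largest BOLD response at 50 ng/mL ketamine", then "Two seeds are placed at (MNI: 4,2,42) and (MNI: -4,2,42) and spherically dilated by 8 mm", and then "For each subject, the BOLD time series is extracted from the ROI and fit to a three parameter gamma model". From the fitted curve it defines two summaries, a peak response and a mean response. It remarks that the two are highly correlated and that the mean is less sensitive to outliers in group comparisons. The section opens by giving a separate MRI manual precedence over its own text, and says that revisions to the manual during the study will be described in the final report.

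Two other sections bear on the point. Under section 8.1.4 the sponsor knows treatment assignment, while those who score the BOLD data are blinded until database lock. Under section 10.5.3 interim ROI results go to the sponsor after every 12 subjects.

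**The concern.** The endpoint is described as resting on pre-specified ROIs, yet the only ROI that the readable protocol specifies carries a different name from either of them. An analyst who follows section 9.3.5.1.3 obtains a mid-cingulate value, no anterior insula value, and nothing labelled ACC. The ACC value needed for exclusion criterion 13 is equally undefined, so it is unclear whether eligibility and endpoint will be read from the same tissue.

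At stake is whether the primary outcome is fixed in advance. If the protocol does not settle the masks and the measure, they are settled in a manual that can change during the study, at a time when an unblinded party is receiving ROI results.

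**Working it through.** No figure in the protocol can be reproduced here: the question is which region is measured, and section 10.1 gives no power calculation. The check sets the sections side by side and then works out what the described mask covers.

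**Regions by section**

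| Protocol section | Purpose | Region(s) named |
|---|---|---|
| 6.2.1 | Primary endpoint | ACC, anterior insula |
| 10.5.1 | Primary ANCOVAs, one per ROI | ACC, anterior insula |
| 7.2, criterion 13 | Eligibility at Final Screening Visit | ACC |
| 9.3.5.1.3 | Mask, extraction, gamma fit | Mid-cingulate cortex only |

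No readable section gives a seed, mask or atlas label for ACC or anterior insula, or equates mid-cingulate with ACC.

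**What the described mask covers**

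Inputs, from section 9.3.5.1.3: centres (4, 2, 42) and (-4, 2, 42), radius r = 8 mm.

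- Distance between centres: d = 4 - (-4) = 8 mm. This is less than 2r = 16 mm, so the spheres merge into one mask.
- Extent: x from -4 - 8 = -12 to 4 + 8 = 12 mm; y from 2 - 8 = -6 to 2 + 8 = 10 mm; z from 42 - 8 = 34 to 42 + 8 = 50 mm.
- Volume of the union: 2 × (4/3)πr³ - π(4r + d)(2r - d)²/12 = 2 × 2145 - π × 40 × 64/12 = 4289 - 670 = 3619 mm³, about 3.6 cm³ before grey-matter weighting. A 0.5 mm grid count gives 3602 mm³.

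This is one midline region and supplies one time series per session. Section 10.5.1 needs at least two.

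**Could this mask serve a primary ROI?**

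- Anterior insula: the mask reaches no further than 12 mm from the midline. The documents give no insula coordinates. On the general anatomical assumption that the insula lies laterally (|x| of roughly 25 mm or more), the mask cannot include it.
- ACC: whether a mask at these coordinates may be called ACC depends on the atlas, which the protocol does not name. The protocol's own label is mid-cingulate.

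**Which measure?**

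Section 9.3.5.1.3 defines peak and mean. Exclusion criterion 13 uses the peak. Section 10.5.1 says only BOLD. The one sentence that compares the two favours the mean for comparing groups, but it does not assign it to the primary analysis.

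**The case against.** The strongest reply is that section 9.3.5.1.3 does not control the extraction. By its own terms the MRI manual takes precedence, and masks and the choice of summary are details that a manual or the SAP commonly holds. The manual is not shown and may define both ROIs exactly. Parts of the background are also redacted, so a rationale for the ROIs cannot be called absent. This stands as far as missing detail goes. It does not remove the conflict, because the protocol does more than stay silent: it states seeds, a radius and a model for a region that the endpoint does not name. A manual that may be revised during the study also leaves the protocol's primary outcome open to change.

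A second reply is that image analysts are blinded (sections 8.1.4 and 9.3.5.1.3), that manual revisions must be reported, and that this is an exploratory phase 1b study with mainly descriptive analyses. These are real safeguards and they lower the stakes. A reader might infer that the choice of mask is wholly unprotected, and the documents do not support that. What remains is that the sponsor is unblinded and receives ROI results after every 12 subjects while the manual is still revisable. Section 10.5.3 does not say whether those results are broken down by treatment group, so the point does not rely on that.

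A reader might also infer that the primary analysis measures the wrong thing. It does not follow: sections 6.2.1 and 10.5.1 agree on ACC and anterior insula. The mismatch lies in the processing text that feeds the analysis.

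**Conclusion.** The point holds as an internal contradiction about the primary outcome. Neither of the two primary ROIs has a matching definition in the readable protocol, the one ROI that is defined is not named as an endpoint, and neither of the two defined BOLD measures is assigned to the ANCOVA. Even if the mid-cingulate mask were accepted as ACC, anterior insula would still have no extraction.

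The contradiction itself needs only the protocol's text. That the mask misses the insula rests on the general anatomical assumption above. Whether it overlaps ACC, and so whether eligibility and endpoint use different tissue, cannot be settled from the documents.

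It is tempting to attach a false-positive rate to this. The documents do not support one. Testing two ROIs and two doses against placebo is a separate multiplicity question that would be unchanged once the ROI text is corrected. Nor can regions and measures be multiplied into a count of independent chances, since the protocol itself calls peak and mean highly correlated.

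**What to change.** Reconcile section 9.3.5.1.3 with sections 6.2.1 and 10.5.1 and with exclusion criterion 13, in one of two ways:

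- If ACC and anterior insula are meant, state both masks (coordinates or atlas labels, radius, hemispheres), use the same ACC mask for exclusion criterion 13, and give mid-cingulate a stated non-primary role.
- If mid-cingulate is meant, correct the endpoint, the primary analysis and the exclusion text to say so.

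In either case, name one BOLD measure as the ANCOVA outcome; the protocol's own remark on outliers favours the mean for group comparison. Fix the ROIs and the measure before the first interim data transfer, which follows the 12th subject, and state that later revisions of the MRI manual do not change them for the primary analysis. If the manual already holds the masks, check it against the endpoint and carry its definitions into the protocol.

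The cost is wording in the protocol and the MRI manual. No scans or subjects are added, and no sample size or power figure changes.

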where  $t_{\max}$  is time of maximum response,  $a$  is amplitude of the response, and  $b$  is the shape parameter of the function. The fitted response is converted to a percent signal change by normalizing to the mean. Peak BOLD response is defined as the maximum value of the fitted gamma model. Mean BOLD response is defined as the area under the curve of the gamma model divided by the scan duration (600 sec). The mean BOLD response is highly correlated to the peak BOLD response but is less sensitive to outliers when comparing groups. A whole brain analysis is performed using multiple linear regression by constructing a gamma regressor with parameters equal to the group mean ( $b = 0.009$ ,  $t_{\max} = 226$  sec). The beta images from the contrast of the first regressor will be used in the group-level analyses.

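### Read literally, peak BOLD is the larger of the fitted amplitude and zero; if peak is the Day 6 outcome, negative fits score 0 and differences between arms shrink

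*Protocol*

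**What the plan says.** Section 9.3.5.1.3 (Image Processing and Modeling) sets out the response model: "For each subject, the BOLD time series is extracted from the ROI and fit to a three parameter gamma model", namely y(t) = a (t/t_max)^(b·t_max) exp((t_max − t)·b). It explains that a "is amplitude of the response, and" b sets the shape. No constraint on the sign of a is stated, and there is no rule for a negative fit.

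Two summaries are then defined:

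- Peak: "Peak BOLD response is defined as the maximum value of the fitted gamma model".
- Mean: "Mean BOLD response is defined as the area under the curve of the gamma model divided by the scan duration (600 sec").

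The section adds: "The mean BOLD response is highly correlated to the peak BOLD response but is less sensitive to outliers when comparing groups".

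The primary endpoint (6.2.1) and the primary analysis (10.5.1) refer only to BOLD in the ACC and anterior insula and choose neither summary. The direction of interest is stated in 10.5.1: "A statistically significant negative change of BOLD found in the active treatment groups compared to placebo group would be consistent with the hypothesis". Peak is put to explicit use in one place, exclusion criterion 13 (7.2). That criterion removes subthreshold ACC responders at the Final Screening Visit, with the threshold "defined as % BOLD signal change of 0.5% at peak ketamine response".

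**The concern.** The hypothesis is that TS-134 lowers the ketamine response. A summary that cannot go below zero is cut off on the side of interest.

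In the ACC, criterion 13 means the cut-off should not bind at baseline, so it can act only on Day 6. It would act most in whichever arm has the smallest response. The anterior insula has no entry threshold, so there it could act at either session.

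If peak were the analysed outcome, these would be at stake:

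- **Estimates.** The adjusted differences and their confidence intervals would move towards zero. Cohen's d in 10.5.1 is scaled by the baseline SD, which in the ACC the floor does not compress. It would shrink in the same proportion as the difference.
- **The 20 mg versus 60 mg comparison.** Both arms may lie near the floor.
- **Agreement of the two summaries.** Peak and mean BOLD would part company in exactly the subjects with the strongest attenuation.

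**Working it through.** **1. Does the floor exist?** Inputs from 9.3.5.1.3: the printed curve, group-mean b = 0.009 and t_max = 226 s, and a 600 s duration. The exponent is b·t_max = 0.009 × 226 = 2.034, which is positive, so y(0) = 0. At t = t_max both other factors equal 1, so y(t_max) = a.

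| a (%) | maximum over 0–600 s | mean BOLD = AUC/600 |
|---|---|---|
| 0.5 | 0.5 (at 226 s) | 0.311 |
| 0.2 | 0.2 (at 226 s) | 0.124 |
| −0.2 | 0 (at 0 s) | −0.124 |
| −0.5 | 0 (at 0 s) | −0.311 |

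The maxima are the same over 0–900 s. Literal peak is max(a, 0), and mean BOLD has no floor.

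**2. How much of a difference could be lost?** The protocol has no figure to reproduce: 10.1 gives no effect size or SD. Suppose the signed Day 6 amplitude is normal with mean m and SD s (in % BOLD). Then E[max(a, 0)] = m·Φ(m/s) + s·φ(m/s). All means and SDs below are assumptions.

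| Placebo m | Active m | s | Active subjects with a < 0 | Signed difference | Floored difference | Lost |
|---|---|---|---|---|---|---|
| 1.0 | 0.5 | 0.3 | 5% | −0.500 | −0.494 | 1.2% |
| 1.0 | 0.25 | 0.5 | 31% | −0.750 | −0.655 | 12.6% |
| 0.8 | 0.2 | 0.7 | 39% | −0.600 | −0.454 | 24.4% |

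Middle row: active 0.25 × 0.6915 + 0.5 × 0.3521 = 0.349; placebo 1.0 × 0.9772 + 0.5 × 0.0540 = 1.004; difference −0.655. In the last row about 13% of placebo subjects are also below zero.

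A wider grid (placebo mean 1.0, active mean 0 to 0.75, SD 0.25 to 1.0) gives losses from about 0% to 32%.

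**3. The dose comparison, same formula, s = 0.5.**

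- Means 0.5 and 0.25: floored 0.542 − 0.349 = 0.193 against 0.25, so 23% is lost.
- Means 0.25 and 0: floored 0.349 − 0.199 = 0.149 (from unrounded values) against 0.25, so 40% is lost.

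**4. Power.** Simulated two-sample t-test, two-sided 0.05, 40,000 runs, with the planned group sizes from 6.1.

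| Comparison | Means | SD | Signed | Floored |
|---|---|---|---|---|
| Placebo (10) v active (25) | 1.0 v 0.5 | 0.5 | 74% | 75% |
| Placebo (10) v active (25) | 1.0 v 0 | 1.0 | 73% | 71% |
| Active (25) v active (25) | 0.4 v 0 | 0.5 | 79% | 72% |
| Active (25) v active (25) | 0.5 v 0 | 0.7 | 69% | 61% |

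The floor reduces variance as well as the difference. The two nearly cancel against placebo but not between two arms close to zero. The t-test stands in for the baseline-adjusted ANCOVA, whose covariate correlation the protocol does not give.

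**The case against.** A reader might infer that the trial's primary measure is floored and so understates attenuation in the active arms. The documents do not support that.

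- Neither 6.2.1 nor 10.5.1 names peak. Section 9.3.5.1.3 leans towards the mean for comparing groups, and the mean is signed. This stands, and it makes the harm conditional.
- The same section calls a the amplitude and t_max the time of maximum response. On that reading peak is the value at t_max, which is a, and signed. The wording allows this, but the stated definition is the maximum of the curve, and the two differ when a < 0.
- The MRI manual takes precedence over this section, and a separate SAP is foreseen. Either may settle the matter, but neither is shown. The protocol's own definition should still be right.
- In the ACC a negative Day 6 fit implies a fall of more than 100% from a baseline peak tied to 0.5%. That is so for a true response, but single-subject fits are noisy. If the response is abolished and the error is symmetric, about half the fits are negative. With mean 0 and SD 0.5 the floored mean is 0.20, not 0.
- The floor acts on placebo too, so only the imbalance between arms biases the contrast. This stands and is built into the figures above.
- The gamma ROI fit is described only for mid-cingulate seeds. Carrying the point over to the insula assumes the same fit is used there.

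A reader might also infer a loss of power to show an effect against placebo. The simulation does not bear that out.

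**Conclusion.** The point holds in conditional form. As a matter of algebra, the stated definition of peak scores every negative fit as 0, and the protocol leaves open whether peak or mean is analysed. If peak is the Day 6 outcome, and negative fits are more frequent in the active arms, then the active-placebo and dose differences, their confidence intervals and Cohen's d are pulled towards zero.

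The size cannot be read from the protocol. The figures of 1% to 24% for the active-placebo difference, and 7 to 8 points of power for the dose comparison, rest wholly on assumed normal amplitudes, means and SDs. Against placebo the harm is to the estimate, not to detection. If mean BOLD is the analysed summary, the floor does not affect the primary result at all. The change is worth making because the correction is nearly free and the choice of summary should be fixed before unblinding.

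**What to change.** In 9.3.5.1.3, define peak BOLD as the signed fitted amplitude a, that is, the fitted value at t_max, with t_max bounded to the post-ketamine scan. Apply the same definition at both sessions, so that decreases score as negative.

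In 6.2.1 and 10.5.1, name signed mean BOLD as the primary summary, on the protocol's own ground that it is less affected by outliers, and signed peak as supportive. Bring the MRI manual into line.

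The cost is a sentence or two in each place. No new data are needed, and for positive fits with t_max inside the scan the peak value is unchanged.

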### 9.3.5.2 Behavioral Assessments

The investigator or a trained designee who is responsible for behavioral assessment scoring will be blinded from any treatment assignment information until the study database is locked.

#### 9.3.5.2.1 Brief Psychiatric Rating Scale (BPRS)

BPRS is a clinician administered rating scale of 20 items that assesses common psychiatric symptoms such as depression, anxiety, and psychotic symptoms. The assessment takes approximately 20-30 minutes to administer.

BPRS will be administered by the investigator or a trained designee at specified timepoints indicated in Sections 9.1 and 9.2. Subjects will be rated outside of the MRI scanner for all timepoints. For post-ketamine ratings, subjects will be instructed to answer questions with regards to their experience during the resting BOLD fMRI scan. Results are to be included in the subject's study record.

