#### **9.2.1.2 Final Screening Visit (First Ketamine Session)**

Following the Initial Screening Visit(s), subjects who meet the initial enrollment criteria will report to the study site for a one-day Final Screening Visit.

During this visit, the following study procedures will be administered to each subject:

- Review of inclusion and exclusion criteria
- Review of prior medication history
- Body weight (kg)
  - Before behavioral assessments
- Physical examination (including a neurological examination)
  - Before behavioral assessments, Discharge
- Vital signs
  - Before behavioral assessments, Discharge
- 12-Lead ECG
  - Before behavioral assessments, Discharge
- C-SSRS – Baseline version
  - Before behavioral assessments
- Saliva alcohol screen
  - Before behavioral assessments
- Urine drug screen
  - Before behavioral assessments
- Urine pregnancy test (all female subjects)
  - Before behavioral assessments
- Ketamine infusion
  - 0 min

- MRI scan
  - 25 min prior to initiation of ketamine infusion: a 7-minute structural scan, a 2-minute phase map, and 2 sets of 30-second BOLD top-up scans
  - 15 min prior to initiation of ketamine infusion: 30-minute BOLD fMRI scan including pre-ketamine (15 minutes) and post-ketamine (15 minutes) scan
- Continuous ECG, pulse oximeter, blood pressure (BP) monitoring
  - throughout the MRI scan
- PK sample collection (ketamine)
  - 5 min post cessation of MRI scan
- BPRS
  - pre-ketamine: 2h prior to initiation of ketamine infusion
  - post-ketamine: immediately following the collection of PK sample for ketamine
- CADSS
  - pre-ketamine: 2h prior to initiation of ketamine infusion
  - post-ketamine: immediately following the collection of PK sample for ketamine
- PGx sample collection (optional)
- Ongoing AE surveillance
- Ongoing concomitant medication for AE inquiry & reporting

Subjects will be discharged following completion of safety procedures described above.

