#### **9.2.2.3 Day 6 (End of Treatment: Second Ketamine Session)**

- Body weight (kg)
  - Pre-infusion
- Physical examination (including a neurological examination)
  - Pre-infusion
- Vital signs
  - Pre-infusion
- 12-Lead ECG
  - Pre-infusion
- C-SSRS – Since Last Visit version
  - 3h post administration of investigational product
- Administration of investigational product
  - 0h

- PK sample collection (MGS0008)
  - 3h post administration of investigational product
- Ketamine infusion
  - 8h post administration of investigational product
- MRI scan
  - 7h 35 min post administration of investigational product: a 7-minute structural scan, a 2-minute phase map, and 2 sets of 30-second BOLD top-up scans
  - 7h 45 min post administration of investigational product: 30-minutes BOLD fMRI scan including pre-ketamine (15 minutes) and post-ketamine (15 minutes) scan
- Continuous ECG, pulse oximeter, BP monitoring
  - throughout the MRI scan
- PK sample collection (ketamine)
  - 5 min post cessation of MRI scan
- BPRS
  - pre-ketamine: 6h post administration of investigational product
  - post-ketamine: immediately following the collection of PK sample for ketamine
- CADSS
  - pre-ketamine: 6h post administration of investigational product
  - post-ketamine: immediately following the collection of PK sample for ketamine
- Ongoing AE surveillance
- Ongoing concomitant medication inquiry & reporting

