### **9.3.5 Pharmacodynamics (PD) Assessments**

#### **9.3.5.1 MRI Assessments with Ketamine Infusion**

BOLD fMRI assessments with ketamine infusion will be conducted at specified timepoints indicated in Sections 9.1 and 9.2. The fMRI scanning time at the second session should be within  $\pm 2$  hour of the scanning time at the first session.

Subjects will be under close observation by an investigator, with visual and verbal contact maintained throughout the MRI session. Subjects who experience distress or become claustrophobic in the magnet will be removed immediately from the magnet room. At least one physician will be present during the course of the procedure. All staff involved in conduct of MRI scan will be thoroughly familiar with the study site's emergency plan.

Total duration of MRI scanning will be approximately 40 minutes. The scanning will be comprised of a 10-minute structural MRI scan (a 7-minute structural scan, a 2-minute phase map, and 2 sets of 30-second BOLD top-up scans), a 15-minute pre-ketamine BOLD fMRI scan, and a 15-minute post-ketamine BOLD fMRI scan. During the 15-minute pre-ketamine BOLD fMRI scan, subjects will receive continuous intravenous administration (i.e., drip) of saline to keep their intravenous line open for subsequent ketamine infusion. Subjects will be under constant monitoring by ECG and pulse oximeter, as well as by frequent BP measurements throughout the MRI scan, which will be recorded in the subject's study records. The make and model of the MRI scanner used, date and time of initiation and cessation of MRI scanning are to be recorded in the subject's study record.

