### 9.3.5.1.2 Image Acquisition

A MRI manual is being provided in a separate document to take precedence over the protocol language in this section. Any revisions to the MRI manual that are implemented during the study will be described in the final report.

Subjects will be scanned using a 3.0T MRI scanner. An approximate 40-minute, eyes-open, resting-state BOLD fMRI scan will be acquired using echo-planar imaging (EPI). A total of 900 image volumes of 23 near-axial slices (4-mm thickness, aligned to the anterior commissure-posterior commissure) will be acquired per session; echo time (TE) = 30 msec; repetition time (TR) = 2000 msec; flip angle = 75°, in-plane resolution = 3.3 mm; matrix size = 64 x 64; field of view (FOV) = 21.1 x 21.1 cm. A T1 weighted SPGR scan will also be acquired (TE = 2.3msec, TR = 2400 msec, flip angle = 12°, 0.8 mm isotropic voxels, matrix size = 300 x 300, FOV = 24 x 24 cm).

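### The recall window for the post-ketamine BPRS and CADSS is not limited to the time after ketamine, and the order of the two scales is not fixed (minor)

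*Protocol*

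**What the plan says.** Sections 9.3.5.2.1 and 9.3.5.2.2 of the protocol have subjects rated outside the scanner at every timepoint. For the later of the two ratings in each session, both sections use the same sentence: "For post-ketamine ratings, subjects will be instructed to answer questions with regards to their experience during the resting BOLD fMRI scan".

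The visit descriptions say what that scan is. At the Final Screening Visit (9.2.1.2) it is a "30-minute BOLD fMRI scan including pre-ketamine (15 minutes) and post-ketamine (15 minutes) scan". Day 6 (9.2.2.3) has a "30-minutes BOLD fMRI scan including pre-ketamine (15 minutes) and post-ketamine (15 minutes) scan". Section 9.3.5.1 describes the first part: "During the 15-minute pre-ketamine BOLD fMRI scan, subjects will receive continuous intravenous administration (i.e., drip) of saline". The same section also lists the parts as two scans: "a 15-minute pre-ketamine BOLD fMRI scan, and a 15-minute post-ketamine BOLD fMRI scan".

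A separate pre-ketamine BPRS and CADSS is planned in each session, nominally 2 hours before the infusion (on Day 6, 6 hours after dosing with the infusion at 8 hours).

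On timing, 9.2.1.2, 9.2.2.3 and footnote d of Table 9-1 place both post-ketamine ratings directly after the ketamine blood sample. Section 9.3.5.2.1 gives 20 to 30 minutes for the BPRS and 9.3.5.2.2 about 5 minutes for the CADSS. No order is stated. Section 9.4 requires the post-ketamine behavioral assessments to keep their time relative to the infusion, but gives them neither an order nor a tolerance.

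**The concern.** Changes in BPRS and CADSS are secondary endpoints (6.2.2), to be analysed by an ANCOVA like that for the primary endpoint (10.5.2). The pre- and post-ketamine schedule suggests that the later rating is meant to capture symptoms under ketamine. An instruction that points to the whole scan lets a subject draw on time before any ketamine was given.

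Two things could follow. Subjects may differ in how they treat the quiet first part of the scan, which adds noise to the change scores, and the placebo group has only 10 subjects. In addition, the first part of the scan is not the same at the two sessions: at screening no study drug has been given, while on Day 6 the subject has received that day's dose. Any direct effect of TS-134 on symptoms in those minutes could enter a score labelled post-ketamine.

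The missing order is a smaller matter of the same kind. If the order of the scales varies between subjects, or between one subject's two sessions, the delay before each scale varies too.

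A recall window cannot be repaired at analysis. Once the ratings are collected, no SAP can separate the two parts of the scan.

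**Working it through.** **1. Length of the scan.** Section 9.3.5.1.2 gives "A total of 900 image volumes of 23 near-axial slices" with "repetition time (TR) = 2000 msec". So 900 × 2 s = 1800 s = 30 minutes. This reproduces the 30 minutes in 9.2.1.2 and 9.2.2.3. It does not match the figure of about 40 minutes that 9.3.5.1.2 gives for the BOLD scan. Section 9.3.5.1 uses 40 minutes for the whole session: 10 structural + 15 + 15.

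**2. Share of the recall window before ketamine, read literally.**
- Nominal: 15 / (15 + 15) = 0.50.
- With the +3-minute allowance in 9.4: 15 / (15 + 18) = 15/33 = 0.45.
- If a subject takes the scan to mean the full 40-minute session: (10 + 15) / 40 = 0.625 precedes ketamine.

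On the narrower reading (the post-ketamine scan only), the share is 0.

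**3. What this could do to a group difference.** The documents do not say how subjects combine moments within the window, so two assumed rules bracket the answer. Let Δk be the difference between groups in symptoms after ketamine, and Δs the difference before it.
- Averaging over time: observed difference = 0.5 Δs + 0.5 Δk. If Δs = 0, half of Δk remains (18/33 = 0.545 with the longer scan).
- Worst moment: if the worst moment falls after the bolus, the observed difference is Δk and nothing is lost.

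The raw difference therefore shrinks by 0 to 50%, depending on the assumed rule.

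**4. What it could do to the standardised difference.** Under averaging, the spread of the ketamine response shrinks as well. With between-subject SD σk for the response and rating noise σe that does not scale:

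standardised difference = 0.5 Δk / √(0.25 σk² + σe²) = Δk / √(σk² + 4 σe²)

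Compared with Δk / √(σk² + σe²), there is no loss when σe is negligible and a halving only when σk is negligible. The protocol gives no SD for either scale and no power calculation (10.1), so no figure inside that range can be supported and none for power is offered.

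**5. Start times of the two scales.** The scan ends nominally 15 minutes after ketamine and the blood sample follows 5 minutes later, at 20 minutes (9.4).
- BPRS first: CADSS starts at 20 + 20 to 20 + 30 = 40 to 50 minutes.
- CADSS first: CADSS starts at about 20 minutes and BPRS at 20 + 5 = 25 minutes.

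Both scales cannot start at 20 minutes, so an order has to be chosen, and the protocol leaves it open.

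**The case against.** The strongest reply is that the intended meaning is plain enough. The instruction applies only to ratings labelled post-ketamine, a pre-ketamine rating already exists in each session, and 9.3.5.1 names the post-ketamine part as a scan of its own. The sentence has a sensible purpose: subjects are interviewed outside the scanner, so it directs them to what they felt inside it rather than at interview. After a bolus given over 1 minute (9.3.5.1.1), a subject has little reason to average the experience with a quiet saline period. The wording is the same in all groups and both sessions, the raters are blinded (8.1.4, 9.3.5.2), and the comparison is between groups and adjusted for baseline. Analyses in this exploratory phase 1 study are described as mainly descriptive (10.3).

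Much of this stands, and it rules out the stronger conclusions that a reader might draw:
- **That the endpoints fail to isolate the ketamine response, or that the effect is halved.** This needs both the literal reading and averaging over time. The protocol compels neither.
- **That the comparison between groups is biased.** A common instruction does not produce this by itself. A direct effect of TS-134 before the infusion on Day 6 could enter the score, but the documents give neither its existence nor its size.
- **That the later scale rates a different period.** Both ratings look back to the scan. A later start lengthens recall but does not change the period being rated.

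Three parts of the reply do not settle the matter. Where the protocol means only the second part of the scan it usually says so (9.3.5.1, 9.3.5.1.1, 9.4), and that qualifier is missing here. Subtracting a rating taken about 2 hours before the infusion does not remove the pre-infusion minutes from the later one. And the MRI manual takes precedence only over image acquisition and processing (9.3.5.1.2, 9.3.5.1.3), not over the behavioral ratings.

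**Conclusion.** The point holds as one of imprecise measurement. The instruction supports two recall windows: about 30 minutes with 50% before ketamine (45% with an 18-minute post-ketamine scan), or about 15 minutes with none. The possible consequence is added noise or dilution in two secondary endpoints. Its size is unknown; the range of 0 to 50% rests wholly on the assumed rating rules above. That the ratings are meant to measure symptoms under ketamine is itself inferred from the schedule, since 5.2 and 6.2.2 do not describe the BPRS and CADSS changes as ketamine-induced. The unstated order of the scales is a small further source of variation. Severity is minor. It is worth correcting because the correction is very cheap and cannot be made after the ratings are collected.

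**What to change.** In 9.3.5.2.1 and 9.3.5.2.2, have subjects rate their experience from the start of the ketamine infusion to the end of the scan, in identical words at the Final Screening Visit and on Day 6. The recall window is then 15 minutes (up to 18) and contains no pre-ketamine time.

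In 9.2.1.2, 9.2.2.3 and footnote d of Table 9-1, state one order for the two post-ketamine scales and use it at both sessions. Taking the 5-minute CADSS first is one practical choice. The BPRS then starts about 5 minutes later, whereas the opposite order delays the CADSS by 20 to 30 minutes.

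The cost is one sentence in each of the two scale sections, an edit to the schedule, and matching rater instructions. No procedure, visit or subject is added, and the sample size is unchanged. If ratings have already begun, apply the new wording only to subjects who have not yet had their first session, so that each subject's two sessions stay comparable.
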